# Bee venom acupuncture for the treatment of chronic low back pain: study protocol for a randomized, double-blinded, sham-controlled trial

**DOI:** 10.1186/1745-6215-14-16

**Published:** 2013-01-14

**Keywords:** Bee venom acupuncture, Chronic low back pain

## Abstract

**Background:**

Chronic non-specific low back pain is the most common medical problem for which patients seek complementary and alternative medical treatment, including bee venom acupuncture. However, the effectiveness and safety of such treatments have not been fully established by randomized clinical trials. The aim of this study is to determine whether bee venom acupuncture is effective for improving pain intensity, functional status and quality of life of patients with chronic non-specific low back pain.

**Methods/design:**

This study is a randomized, double-blinded, sham-controlled clinical trial with two parallel arms. Fifty-four patients between 18 and 65 years of age with non-radicular chronic low back pain experiencing low back pain lasting for at least the previous three months and ≥4 points on a 10-cm visual analog scale for bothersomeness at the time of screening will be included in the study. Participants will be randomly allocated into the real or sham bee venom acupuncture groups and treated by the same protocol to minimize non-specific and placebo effects. Patients, assessors, acupuncturists and researchers who prepare the real or sham bee venom acupuncture experiments will be blinded to group allocation. All procedures, including the bee venom acupuncture increment protocol administered into predefined acupoints, are designed by a process of consensus with experts and previous researchers according to the Standards for Reporting Interventions in Clinical Trials of Acupuncture. Bothersomeness measured using a visual analogue scale will be the primary outcome. Back pain-related dysfunction, pain, quality of life, depressive symptoms and adverse experiences will be measured using the visual analogue scale for pain intensity, the Oswestry Disability Index, the EuroQol 5-Dimension, and the Beck’s Depression Inventory. These measures will be recorded at baseline and 1, 2, 3, 4, 8 and 12 weeks.

**Discussion:**

The results from this study will provide clinical evidence on the efficacy and safety of bee venom acupuncture in patients with chronic non-specific low back pain.

**Trial registration:**

This study is registered with the United States National Institutes of Health Clinical Trials Registry: NCT01491321

## Background

Chronic non-specific low back pain (CLBP) is a common medical problem considered as a multifactorial disorder in which musculoskeletal pain and psychosocial factors interact with each other [1,2]. The socioeconomic impact of CLBP is related to its greater comorbidities and more frequent prescriptions of pharmacotherapies and other adjunctive medications associated with these painful conditions [3]. Despite of variable accessibility to conventional treatments, patients with low back pain (LBP) have increasingly been using complementary and alternative medicine to alleviate their symptoms [4]. The tendency towards the use of complementary and alternative medicine in CLBP may reflect the deficits and unfulfilled patient expectations in conventional medical treatment [5]. Therapeutic modalities of complementary and alternative medicine, including acupuncture, herbal medicine, thermal therapy and spinal manipulative therapy, have been used in patients with CLBP [5,6] but evidence of effectiveness has not been fully established.

Bee venom acupuncture (BVA) involves injecting purified and diluted bee venom into acupoints [7]. BVA exhibits several pharmacological actions, including analgesic, anti-inflammatory, anti-arthritic, and anti-cancer effects through multiple mechanisms, such as activation of the central inhibitory and excitatory systems and modulation of the immune system [8]. The analgesic effects of BVA have been reported in animal experiments [9,10] and in the clinic [7,11]. Researchers have found that BVA could be a therapeutic option for alleviating LBP [7,12]. Recently, a cohort study revealed that the bee venom integrative package, which comprises herbal medicines, acupuncture and spinal manipulation, is effective in the treatment of LBP with leg pain [13]. However, there has been relatively little evidence in clinical trials on BVA to treat CLBP, especially rigorous randomized controlled clinical trials on the efficacy of BVA. Therefore, a rigorous randomized controlled trial is needed to develop clinical indications and a manual for the optimal practical guidelines of BVA.

### Aims

The purpose of this study is to determine whether BVA is effective at improving pain intensity, functional status and quality of life in patients with CLBP.

## Methods/design

### Design

This study is a randomized, double-blinded, sham-controlled clinical trial with two parallel arms. We intend to compare the effects of BVA and pharmacotherapy with sham-BVA and pharmacotherapy in patients with CLBP. The trial is registered with the U.S. National Institutes of Health Clinical Trials registry and is approved by the Institutional Review Board of Kyung Hee University Hospital at Gangdong (KHUHGD). The outcome assessment and the statistical analyses are performed by professionals who are blinded to the assignment of patients to the real or sham BVA group.

### Participants

Patients with non-radicular chronic LBP will be recruited with a target sample size of 54 participants.

Inclusion criteria:

Being between 18 and 65 years of age

Experiencing LBP lasting for at least the previous three months

Scoring ≥4 points on a 10-cm visual analog scale (VAS) for bothersomeness of LBP at the time of screening

Exhibiting no abnormalities on neurological examination (for example, lumbosacral nerve function, deep tendon reflexes, plantar response, voluntary muscle activation and sensory function)

Having non-specific, uncomplicated LBP, that is, International Classification of Diseases-10 codes:

M513 Other specified intervertebral disc degeneration

M545 Low back pain

M548 Other dorsalgia

M549 Dorsalgia, unspecified

S335 Sprain and strain of lumbar spine

S337 Sprain and strain of other and unspecified parts of the lumbar spine and pelvis

S336 Sprain and strain of sacroiliac joint

Agreeing to participate and signing informed consent

Exclusion criteria:

Radicular pain

Serious spinal disorders, including malignancy, vertebral fracture, spinal infection and inflammatory spondylitis

Other chronic diseases that could affect or interfere with the therapeutic outcomes, including cardiovascular disease, diabetic neuropathy, active hepatitis, fibromyalgia, rheumatoid arthritis, dementia and epilepsy

Previous spinal surgery or scheduled procedures during the study

Painful conditions induced by traffic accidents

Chief musculoskeletal pain other than back pain

Conditions where BVA might not be safe, including clotting disorders, administration of an anticoagulant agent, pregnancy and seizure disorders

Documented hypersensitive reactions to previous BVA treatments, bee stings or insect bites

Severe psychiatric or psychological disorders

Current use of corticosteroids, narcotics, muscle relaxants or herbal medicines to treat LBP or any medication considered inappropriate by the investigator

Pending lawsuit or receipt of compensation because of LBP

Refusal to participate in the trial or provide informed consent

Inability to read and write in the Korean language

### Recruitment

Participants will be recruited through advertisements in local newspapers, on hospital websites and on bulletin boards. If patients are interested in participation, they will be asked to answer screening questions to determine their eligibility. If eligible, they will be guided through the informed consent process. After written consent is obtained, a study researcher will administer the baseline questionnaire then randomly allocate the participants into the real or sham BVA group. After randomization, the interviewer will schedule the treatment procedure. All recruit procedures will be recorded in a log file (Figure 1).

**Figure 1 F1:**
[figure not shown]
**Study sequence.** Process of recruitment, randomization to treatment and outcome assessment.

### Randomization and blinding procedure

Randomization will be undertaken through a computerized software randomization program by an independent statistician who is concealed with respect to the patients. Randomization will be performed only after a participant is confirmed to be eligible and written informed consent has been obtained. Participant details will be recorded, and the treatment arm and randomization number will be allocated to the patients; both of these are included in the participants’ hospital files. The randomization form will be completed and returned to the principal investigator.

As a double-blinded randomized controlled trial, the researcher performing the outcome measure assessments will be blinded to the patient’s treatment allocation. Furthermore, the people who administer treatments will be blinded as to whether the patient receives real or sham BVA, and the pharmacopunctures will be prepared by independent researchers.

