## Discussion

The results from this study will determine the efficacy and safety of BVA on CLBP as an adjunctive treatment to pharmacotherapy that reflects daily practice. These results can provide clinical evidence regarding whether BVA can be beneficial in pain alleviation and changing disease-related functional status.

Previous randomized clinical trials that compared the efficacy of BVA with acupuncture or normal saline injection on LBP [29,30] have been underestimated due to their poor methodological quality. In this study, participants from both the real and sham BVA groups will be treated by the same protocol to minimize the non-specific and placebo effects. All procedures (including the BVA increment protocol administered into predefined acupoints) have been rigorously designed by a process of consensus with experts and previous research according to the Standards for Reporting Interventions in Clinical Trials of Acupuncture. However, the blinding and allocation concealment could be compromised by the manifestation of a bee-venom-specific response in patients in our experimental group, including pain, swelling, redness of the skin and itching, which could be perceived by patients. We will try to blind and conceal group allocation between patients, assessors, acupuncturists and researchers by having an independent researcher prepare both real and sham BVA procedures. The results of this trial will be available in August 2013.

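### The treatment arm itself, not only the randomization number, is to be filed in each participant's hospital record, which contradicts and puts at risk the blinding claimed for assessors and treating staff.

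*Protocol article*

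**What the plan says.** All references are to the protocol article.

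- **What is recorded.** The section Randomization and blinding procedure says that "the treatment arm and randomization number will be allocated to the patients; both of these are included in the participants’ hospital files". It then adds: "The randomization form will be completed and returned to the principal investigator". It does not say what that form shows.
- **Who is blinded.** The same section says that "the researcher performing the outcome measure assessments will be blinded to the patient’s treatment allocation" and that "the people who administer treatments will be blinded as to whether the patient receives real or sham BVA". The Methods/design paragraph of the abstract is wider: "Patients, assessors, acupuncturists and researchers who prepare the real or sham bee venom acupuncture experiments will be blinded to group allocation". Table 1, item 6(b), also has assessor, acupuncturist and patients unaware of the allocation. The Discussion describes an intention: "We will try to blind and conceal group allocation between patients, assessors, acupuncturists and researchers by having an independent researcher prepare" both the real and the sham material.
- **Who allocates.** Under Recruitment, "a study researcher will administer the baseline questionnaire then randomly allocate the participants into the real or sham BVA group". The later section on randomization and blinding says instead: "Randomization will be undertaken through a computerized software randomization program by an independent statistician who is concealed with respect to the patients".
- **Who prepares.** The abstract counts the preparers among the blinded. The randomization section calls them independent and says nothing about whether they know the contents.

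**The concern.** A blinded trial usually keeps the link between randomization number and arm away from anyone who treats or assesses. Here the text directs that the link be written into the hospital record. A condensed article may well leave out a safeguard. This is different: it is a stated procedure that works against the blinding claimed a few lines later.

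Three features of the trial make a leak matter:

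- Under Data collection and under Withdrawal and dropout, the attending doctors determine when participation ends. Those decisions decide which values are carried forward in the intention-to-treat analysis and who remains in the per-protocol analysis (Data analysis).
- Under Bee venom treatment protocol, acupuncturists choose up to ten points per session and may vary them with symptoms.
- The primary outcome is a patient's own rating of bothersomeness, which could respond to cues from staff who know the arm.

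**Working it through.** There is no figure to reproduce and no arithmetic applies. The check sets the statements side by side.

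**1. The hospital file against the blinding claim.**
- Recorded: arm and number, with the text stating that both go into the file. This excludes a reading in which only a code is filed.
- Claimed: assessors and treating staff blinded (same section), also patients and preparers (abstract).
- Access: not described. No sealing, coding or restriction is mentioned.
- Result: the two statements are compatible only if the arm entry is shielded from assessors and treating staff, and the article does not say that it is. As written, the arm is on record for every participant, 54 if recruitment reaches target. That counts records made, not staff unblinded.

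**2. The form returned to the principal investigator.**
- Stated: a completed randomization form is returned.
- Not stated: that the form carries the arm.
- The principal investigator is not listed as blinded in the abstract or in the randomization section. The Discussion's reference to researchers might include that role, or might only echo the abstract's researchers who prepare the injections.
- Result: no contradiction is shown. Keeping the arm off the form is a precaution.

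**3. Who allocates.**
- Recruitment: the study researcher who gives the baseline questionnaire also allocates. Baseline measures include the primary outcome (Table 2).
- Randomization and blinding procedure: an independent statistician randomizes, and only after eligibility and consent are confirmed.
- Result: the statements conflict as worded. They agree if the statistician runs the program and holds the list while the researcher enrols and obtains the assignment. The article does not say so. Even on that reading, the researcher should receive a number, not an arm.

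**4. Who knows the contents.**
- Abstract: preparers are blinded. Randomization section: preparers are independent.
- The venom is diluted and filtered at the hospital's pharmacy (Bee venom treatment protocol), and the sham is plain saline (Treatment details).
- Result: the statements agree if the pharmacy supplies coded stock and others fill the syringes. No coded stock is described. Someone in the chain must know the contents, and the article does not say who.

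**5. Size.** The bias depends on how many staff saw the arm and how far that changed their conduct. The document gives neither, so no figure can be derived.

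**The case against.** The strongest defence is that recording is not exposure. The article does not say who reads the hospital files, and the full protocol may restrict the entry. That stands, and it limits the conclusion to a contradiction and a risk. It does not remove the point, because a direction to file the arm is not a detail lost in condensing.

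Several stronger readings are tempting, and the document does not support them:

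- *Blinding is defeated.* No statement says that assessors or treating staff consult the entry.
- *The principal investigator is told the arm, and this breaks the blind.* The contents of the form are not given, and that role is not clearly among those called blinded.
- *Allocation concealment fails.* Concealment concerns foreknowledge before enrolment. Randomization follows eligibility and consent, and an entry made afterwards does not by itself reveal that participant's assignment in advance. The two statements on who allocates have a consistent reading.
- *The preparers cannot be blinded.* With coded stock from the pharmacy they could be.
- *Attending doctors judge whether adverse events are treatment-related.* The Safety section gives the investigation of adverse events to the research team.

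It is also fair to say that the primary outcome is rated by the patient, so any effect through staff is indirect. The Discussion already admits that local venom reactions may reveal the arm, and that route would remain after this change. But reactions give an uncertain clue once treatment has started, whereas the file gives the exact arm from randomization and is wholly avoidable.

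**Conclusion.** The point holds for the hospital file. Placing the arm there without a stated restriction contradicts the blinding claimed for assessors and treating staff, and puts it at risk. Because the title calls the trial double-blinded and the remedy is simple, this should be corrected. The possible bias, through withdrawal decisions, choice of points and cues to patients, cannot be quantified from the document. The conclusion assumes only that a hospital file can be reached by the staff who treat or assess the patient. If the full protocol already seals the entry, the remaining fault is the wording of the article.

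The conflicting statements on who allocates and on whether preparers are blinded need alignment. They do not show that concealment or blinding has failed.

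**What to change.** 1. In Randomization and blinding procedure, have the hospital file carry only the randomization number. As a precaution, do the same for the form returned to the principal investigator.
2. State that the code-to-arm list is held by the independent statistician and by whoever in the pharmacy or preparation role must know it, with sealed individual codes for emergencies. The Design section calls those who do the statistical analyses blinded, so the list-holder should not be the analyst.
3. The Trial status section says recruitment is under way. For participants already randomized, seal or remove the arm entry.
4. Align Recruitment with the randomization section: say who generates the sequence, who enrols and who assigns, with the study researcher receiving only a number.
5. Reconcile the abstract (preparers blinded) with the randomization section (preparers independent) by stating who knows the contents of the syringes.

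The cost is small changes to forms and wording, plus a check of files already opened. The statistician, the pharmacy and the independent preparers are already in the plan.

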### Education of acupuncturists

Licensed Korean medical doctors (KMDs) who are specialized in acupuncture and moxibustion or oriental rehabilitation medicine will take an educational course to ensure their strict adherence to the study protocol and familiarity with administering study treatments; all participating KMDs will undergo intensive and customized training for a full understanding of the BVA increment protocol, including details such as acupuncture points and weekly dose increments of pharmacopuncture.

### Description of all interventions and comparisons

#### Treatment details

Both the real and sham BVA groups will receive a total of six pharmacopuncture sessions over three weeks. In the BVA group, 26-gauge sterile disposable syringes (Noksipja, Seoul, Korea) containing bee venom diluted with normal saline (0.9% NaCl) will be used, whereas normal saline without bee venom with the same dose will be used in the sham BVA group. A skin hypersensitivity test will be performed on all the patients at LI 11 acupoints with subcutaneous injections of 0.05 ml of 1:20,000 bee venom preparation. Local swelling over 10 mm in diameter or redness over 20 mm in diameter will be considered positive reactions, and these patients will be excluded from this study. At the first pharmacopuncture session, all participants will receive a copy of the *Exercise Manual for Patients with Low Back Pain* from the spine center of KHUHGD and will be encouraged to exercise according to the manual during the entire treatment period. As a rescue therapy to minimize the risk of disease deterioration during the trial period, all the participants will be prescribed loxonin (Loxoprofen, 60 mg/tablet; Dong Wha Pharm Co., Ltd., Seoul, Korea) per os one tablet three times a day throughout the treatment period.

#### Bee venom treatment protocol

BVA will be prepared as dried bee venom powder (Yoomil Garden, Hwasun, Korea) then diluted and filtered in normal saline (1:20,000) at the Traditional Korean Medical Pharmacy at KHUHGD. After sterile skin preparation, patients from both real and sham BVA group will be subcutaneously injected perpendicularly at a depth of 0.5 cm to 1.0 cm with the patient lying in a prone position. Pharmacopuncture will be prepared by a predefined weekly incremental protocol as follows; 0.2 ml for the first week, 0.4 ml for the second week and 0.8 ml for the third week. Patients in the sham BVA group will be injected with the same volume as those in the BVA group. The predefined points are carefully selected by a process of consensus among participating KMDs who are all experienced in the treatment of LBP. Acupuncturists can select up to 10 points from predefined acupoints as a reflection of daily practice, in which the acupuncture points are varied based upon changes of patient symptoms or pain (Table 1).

**Table 1 T1:** Bee venom acupuncture treatment and sham treatment protocol

	**Item**	**Details**
1. Acupuncture rationale	(a) Style of acupuncture	Traditional Korean medicine theory
	(b) Reasoning for treatment provided (based on historical context, literature sources and consensus methods)	Textbook on acupuncture and moxibustion-related articles (published trials) [14]
	(c) Extent to which treatment was varied	Within 10 predefined acupoints
2. Details of needling	(a) Number of needle insertions per patient per session	Within 10 acupoints
	(b) Names (or location if no standard name) of points used (uni/bilateral)	Shenshu (BL23), Qihaishu (BL24), Dachangshu (BL25), Huantiao (GB30), Yaoyangguan (GV3), Mingmen (GV4), Xuanshu (GV5)
	(c) Depth of insertion	5 to 10 mm (subcutaneous)
	(d) Response sought (for example, *de qi* or muscle twitch response)	Penetrating, sharp, aching and painful sensations when penetrating the skin. Spreading and lumpish sensation around the injection site. Skin stimulation by bee venom in BVA group.
	(e) Needle stimulation (for example, manual, electrical)	Pharmacopuncture
	(f) Needle-retention time	None
	(g) Needle type (diameter, length and manufacturer or material)	1.0 ml disposable syringe (26-gauge needle) produced by Green Cross Medical Equipment (Seoul, Korea)
3. Treatment regimen	(a) Number of treatment sessions	Six
	(b) Frequency and duration of treatment sessions	Twice a week for three weeks
4. Other components of treatment	(a) Details of other interventions administered to the acupuncture group	Brochure with information about chronic low back pain, lifestyle advice
	(b) Setting and context of treatment, including instructions to practitioners and information and explanations to patients	Independent researcher counseling regarding treatment, lifestyle management of low back pain
5. Practitioner background	(a) Description of participating acupuncturists	Korean medical doctors who are specialists of acupuncture and moxibustion or oriental rehabilitation medicine, with more than three years of clinical experience under supervision by a specialist
6. Control or comparator interventions	(a) Rationale for the control or comparator in the context of the research question with sources that justify this choice	See [15]
		See [16]
		See [17]
	(b) Precise description of the control or comparator if sham acupuncture	**Double blind:** In the sham BVA group, normal saline was used instead of BVA. Both real and sham BVA were subcutaneously injected into predefined acupoints through identical manipulation techniques and the assessor, acupuncturist and patients were uninformed about allocation.
		**Explanations given to patients:** Explanation of real or sham BVA was given to patients before randomization.
		**Details of sham BVA:** Acupuncture points used, needle type, depths of insertion, responses, needle stimulation and needle retention time were identical in each group. The only difference was that normal saline was used for injection.
		**Injection and increment protocol:** The BVA group was prepared by a predefined weekly increment protocol as follows: 0.2 ml for the first week, 0.4 ml for the second week and 0.8 ml for the third week. The sham BVA group was injected with normal saline at the same volume as the BVA group. The predefined points were carefully selected by a process of consensus with the participating Korean medical doctor.

BVA: bee venom acupuncture.

